### Sample collection

Tumor tissue, blood, urine, and stool specimens for translational biomarker research will be sampled at the baseline visit, during surgery, 3 months after induction therapy, and 3 months after maintenance therapy. Embedded future studies will have their specific protocol and will obtain specific approval from the ethics committee separately. The tumor tissue from the participants will be obtained from a core needle biopsy sample (20 mg) or a surgically excised sample (1 g) of the viable tumor portion confirmed by the pathologist. Blood (10 mL for plasma) will be drawn when a medically required blood draw is present. Midstream urine (10 mL) and fecal (2–3 cc) samples will be collected from patients using the information leaflet provided. Samples will be collected 3–4 times, and an overview of the planned sample collection is shown in Tables 2, 3, and 4. All samples will be anonymously labeled with a pseudo-patient study identifier.

**Table 2 Tab2:** Study schedule of visits, and sampling of upfront cytoreductive nephrectomy group (Group A)

Time	0	*X*	*X* + 4 months	*X* + 7 months
Visit	Baseline visit	During surgery	After ICI induction phase (4 cycles)	After ICI maintenance phase (6 cycles)
Blood sample	O	O	O	O
Urine sample	O	O	O	O
Stool sample	O	O	O	O
Tumor tissue sample	O	O

**Table 3 Tab3:** Study schedule of visits, and sampling of deferred cytoreductive nephrectomy group (Group B)

Time	0	*X*	*X* + 3 months	*X* + 4 months	*X* + 7 months
Visit	Baseline visit	Before ICI therapy	After ICI induction phase (4 cycles)	During surgery	After ICI maintenance phase (6 cycles)
Blood sample	O		O	O	O
Urine sample	O		O	O	O
Stool sample	O		O	O	O
Tumor tissue sample	O			O

**Table 4 Tab4:** Study schedule of visits, and sampling of immune checkpoint inhibitor therapy group (Group C)

Time	0	*X*	*X* + 3 months	*X* + 6 months
Visit	Baseline visit	Before ICI therapy	After ICI induction phase (4 cycles)	After ICI maintenance phase (6 cycles)
Blood sample	O		O	O
Urine sample	O		O	O
Stool sample	O		O	O
Tumor tissue sample	O			

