### Statistical analysis

Descriptive statistics will be used to assess clinicopathological characteristics. Mean values and standard deviation will be provided for continuous variables, whereas frequency and percentage distributions will be provided for categorical variables. Groups will be compared using the chi-square test for categorical variables and the Student’s *t*-test for continuous variables. The Kaplan–Meier and log-rank test method and log-rank test will be used to estimate and compare OS and PFS. Univariate and multivariate survival analyses will be conducted using the Cox proportional hazards model, which will provide hazard ratios (HRs) with 95% confidence intervals (CI). For subjects without endpoints or who violate the study protocol will be excluded. Statistical analysis will be performed using SPSS software (version 25.0; IBM, Armonk, NY) and R software [V.3.6.2 (http://www.R-project.org)]. The significance level will be set at *P* < 0.05, and all statistical tests will be two-sided.

Microbiome analyses will be conducted using 16S rRNA sequencing to determine the differences in alpha diversity among the three groups by calculating the Shannon, Chao1, and Simpson indices. Beta diversity will be generated using the weighted UniFrac distance and visualized using a principal component analysis plot. Between-group differences were analyzed using multivariate analysis of variance with permutation. Furthermore, subgroup analysis according to the number and location of metastasis will be performed.

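### The three-group microbiome comparison names no stool visit and no use of the baseline stool, although treatment contrasts change from visit to visit and A versus C is never randomised

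*Protocol article*

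**What the plan says.** The microbiome paragraph of the Statistical analysis section says that 16S sequencing will be used "to determine the differences in alpha diversity among the three groups by calculating the Shannon, Chao1, and Simpson indices". Beta diversity is to be based on weighted UniFrac distance, and then: "Between-group differences were analyzed using multivariate analysis of variance with permutation". No visit, model or covariate is named for either. The only test named in that section for a continuous variable is in the preceding paragraph on clinicopathological characteristics: "Groups will be compared using the chi-square test for categorical variables and the Student’s" *t*-test.

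The Sample collection section says that specimens "will be sampled at the baseline visit, during surgery, 3 months after induction therapy, and 3 months after maintenance therapy", and that "Samples will be collected 3–4 times". Tables 2–4 give the detail by group. All three groups have a stool sample at baseline, after induction and after maintenance. Groups A and B also have one at surgery.

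The Group-specific criteria give the order of treatment: nephrectomy before induction in A, between induction and maintenance in B, and never in C. The Study timeline forms the groups in two steps. Patients operable at the first visit are randomised to A or B. The others start induction and are then reassessed. Those now operable are randomised to B or immunotherapy only, and those still inoperable go to C without randomisation.

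**The concern.** A difference among the three groups has a different meaning at each visit, and at one of them it has none. If the visit is chosen after the data are seen, the question being answered is chosen with it.

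Diversity also varies between people before any treatment. In small groups, an unadjusted follow-up difference partly reflects who is in each group. Here that goes beyond chance, because operability decides who can enter A and who is placed in C. A baseline stool from every patient would absorb part of this variation, but the article assigns it no role.

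At stake is the precision and interpretation of an exploratory result. The Discussion nonetheless ties that result to biomarkers for selecting patients for nephrectomy. Overall survival is not affected.

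**Working it through.** **Step 1: the plan's own figure.** The article gives no power, standard deviation or correlation for diversity. Its only design calculation is for survival, and it reproduces:
- Events: (1.96 + 0.84)² / (0.66 × 0.34 × (ln 0.37)²) = 35.4, against 35 stated.
- Five-year event probabilities, with rates of 0.53 and 0.37 × 0.53 and censoring at 0.1: 0.805 (immunotherapy only) and 0.512 (nephrectomy), a weighted average of 0.611.
- Patients: 35 / 0.611 = 57.2, against 57 stated.

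This does not bear on the microbiome plan except to supply the total of 57.

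**Step 2: treatment received by each stool visit** (Tables 2–4 with the Group-specific criteria; CN = nephrectomy).

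| Stool visit | A | B | C |
|---|---|---|---|
| Baseline | untreated | untreated | untreated |
| Surgery | before immunotherapy | after induction | none |
| After induction | CN, induction | induction | induction |
| After maintenance | CN, induction, maintenance | induction, CN, maintenance | induction, maintenance |

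Treatment therefore differs at two shared follow-up visits. After induction, A differs from B and C. After maintenance, all three sequences differ, and this is the only shared visit at which B differs from C.

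**Step 3: which contrasts are randomised** (Study timeline). A versus B is randomised among patients operable at the first visit. B versus C is randomised among patients found operable after induction. A versus C is never randomised.

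**Step 4: how many patients each randomised contrast can have.** Assume that the planned shares hold and that both steps allocate 1:1. Then 0.66 × 57 = 37.6 patients are in A and B together, and 0.34 × 57 = 19.4 are in C. With a patients per arm randomised at the first visit and b per arm after induction, 2a + b = 37.6 and b ≤ 19.4. So a = 18.8 if b = 0, a = 9.1 if b = 19.4, and a = b = 12.5 in the balanced case. About 19 per arm is the ceiling for either contrast, and both cannot reach it. Deaths and dropouts lower these numbers further, and the Dropout criteria include starting corticosteroids or antibiotics.

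**Step 5: gain from the baseline value.** With baseline as covariate, residual variance is multiplied by 1 − r², where r is the baseline-to-follow-up correlation (assumed). The difference detectable with 80% power at two-sided 0.05 is 2.80 × √(1 − r²) × √(2/n), in SD units, by normal approximation.

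| r | 1 − r² | n = 19 per arm | n = 12 per arm |
|---|---|---|---|
| unadjusted | 1.00 | 0.91 | 1.14 |
| 0.3 | 0.91 | 0.87 | 1.09 |
| 0.5 | 0.75 | 0.79 | 0.99 |
| 0.7 | 0.51 | 0.65 | 0.82 |

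For a true difference of 0.8 SD with 19 per arm, power is 69% unadjusted and 73%, 81% and 93% adjusted. Simulation with t-based tests gave 67–68% unadjusted and 69%, 80% and 91% adjusted.

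**Step 6: timing.** Four cycles three weeks apart take about 12 weeks, so the post-induction visit at X + 3 months in Tables 3 and 4, where X is the start of immunotherapy, is the end of induction. Read literally, the text places that sample three months after induction. In Group B that is later than the surgery at X + 4 months, so B and C would no longer have been treated alike. Step 2 follows the tables.

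**The case against.** The strongest reply is that the article is silent rather than wrong. It does not say that diversity is compared without adjustment, that baseline is discarded or that visits are pooled. The *t*-test belongs to the clinicopathological descriptives, and a permutation analysis of variance can carry covariates. Visit and covariate for an exploratory 16S analysis may well be settled in a fuller document. The microbiome work is not a primary or secondary endpoint, and the Discussion concedes that the small sample limits biomarker conclusions.

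Much of this stands. A reader might infer that the plan commits to raw comparisons or mixes unlike samples; the text supports neither. A reader might also infer that the groups differ in treatment at only one shared visit. Step 2 shows two, and only the narrower statement, that all three differ from one another at one visit, is true.

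What survives is that the article does state the contrast, among three groups. At the surgery visit that contrast does not exist, after induction it reduces to A against two identically treated groups, and after maintenance it includes a pair that was never randomised. Matching contrasts to visits is therefore a substantive change and not a request for more detail.

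**Conclusion.** The concern holds as a minor point. The stated three-group comparison should be tied to visits and to the randomised pairs, and the baseline stool should be used.

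The gain in precision is r squared of the residual variance: 9%, 25% and 49% at r = 0.3, 0.5 and 0.7. That range is assumed, since the documents give no r. It would be tempting to express the gain as a larger effective sample built on all 57 patients. That is not supportable, because each randomised contrast uses at most about 38 (two arms of about 19).

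Nor does adjustment turn the three-group comparison into a randomised one. It reduces noise and part of any pre-treatment difference in diversity, but not the selection by operability that separates A from C. This rests on the two-step allocation in the Study timeline; the Abstract describes random allocation to three groups. The reading of the post-induction visit rests on Tables 2–4 rather than on the sampling text.

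**What to change.** In the microbiome paragraph, state that:
- each alpha-diversity index at follow-up is analysed with the patient's own baseline value as covariate;
- A is compared with B after induction, among patients randomised at the first visit;
- B is compared with C after maintenance, among patients randomised after induction;
- any three-group comparison after maintenance is reported as exploratory and non-randomised;
- the UniFrac permutation test uses the same visits and patient sets;
- surgery samples are described but not entered in between-group tests.

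The Abstract also promises analysis of the urine community, and urine follows the same schedule, so the same visit rules can apply there.

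Separately, reconcile the sampling times in the Sample collection text with the post-induction visit in Tables 2–4, because whether B has had surgery by that sample depends on it.

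The cost is a change of analysis wording. The baseline stool is already scheduled and no new data are needed. Patients without a baseline stool drop out of the adjusted analysis, and the randomised contrasts are smaller than the full groups.

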### Interim analyses

The data management and monitoring team monitors safety outcomes and provides recommendations regarding the continuation or premature termination of the trial. No interim analyses concerning efficacy are performed. We planned two interim statistical analyses on safety during the course of this study, after approximately 25% and 50% of the inclusion. The only stopping condition is based on safety. The decision to stop or continue is made by the trial team based on the advice of the data management and monitoring team. The risk of life-threatening immune-related adverse complications will be evaluated.

### Data management and checks

The data management and monitoring team will be responsible for overseeing the receiving, entering, cleaning, querying, analyzing, and storing of all data that accrues from the study by designated persons. Each month, this team will randomly check the files in all three centers. Furthermore, daily monitoring of the data will be done by the members of the study coordinating center to minimize entry errors. All data will be stored on access-controlled computers and servers in line with data security policies. Databases will be backed up monthly.

### Adherence with study protocol

Non-adherence with the trial protocol will be reported and will be dropped out from the study.

### Missing data

Missing data will be minimized by performing a thorough data cleaning process until data are either received, confirmed as unavailable or the trial has reached the analysis stage. If missing for less than 5% of participants, these missing values will be imputed using mean or median values (depending on the distribution of non-missing data) for the whole cohort. If missing for more than 5% of participants, then multiple imputation will be considered.

## Ethics and dissemination

### Ethics

The study has been approved by the Institutional Review Board (IRB) of the YUHS (approval nos.4–2022-1453, 2023–0318-001, 2022–0618-001) and will be performed in accordance with the principles enunciated in the current version of the Declaration of Helsinki. Each substantial protocol amendment will be notified for approval to the IRB of the YUHS prior to implementation.

### Dissemination plan

Upon completion of the study, we intend to present the results as oral communications and abstracts at national and international urological meetings. The results will be published in a peer-reviewed journal. Publication policy of this trial has been negotiated and specified in contractual obligations and agreements between involved investigators.

## Discussion

The optimal use of CN in mRCC settings remains unclear, especially in ICI therapy settings [19], where the most recent evidence has been generated in the TKI era [19]. Although the potential of CN in the primitive IO era has drawn attention, no studies have thoroughly evaluated the role of CN in ICI therapy in patients with mRCC, where recent guidelines have moved away from TKI monotherapy in favor of ICI-based combinations. This is the first study to comprehensively incorporate both upfront and deferred CN and compare both with ICI therapy, redefining the role and timing of surgeries in mRCC. Because oncologic surgery can effectively control cancer by removing tumor cells [20], it should be considered as a treatment option for mRCC in selected patients, weighing the benefits and risks tailored to each patient. Moreover, CN may reduce the cost of ICI therapy, allowing for therapeutic holidays [19]. As patient selection is critical for expanding the role of CN in the contemporary IO era [21], the objective of this study is to develop biomarkers for patient selection for CN by analyzing gene mutation profiles and microbiomes. Due to the small number of study population, there could be some difficulties in drawing conclusions for discovery of biomarkers. Therefore, we will first achieve our primary endpoint, OS, and will expand the study for other analysis. Furthermore, the decision to perform CN should be discussed by a multidisciplinary team and clearly explained to the patients during shared decision-making sessions.

This study was registered at ClinicalTrials.gov on March 3, 2023. Patient accrual began in December 2022. Follow-up will be performed for at least 5 years or until death.

## Trial status

Recruitment of participants started in July 2023 and will be completed in December 2027. The manuscript reports protocol version 1.0 (January 2, 2023).

## Data Availability

The datasets generated and/or analyzed during the current study are available from the corresponding author on reasonable request.

## Abbreviations

CN: Cytoreductive nephrectomy
RCC: Renal cell carcinoma
mRCC: Metastatic renal cell carcinoma
IO: Immuno-oncology
CPI: Checkpoint inhibitor
IMDC: International mRCC Database Consortium
ST: Systemic therapy
ICIs: Immune checkpoint inhibitors
TKI: Tyrosine kinase inhibitor
RCTs: Randomized clinical trials
OS: Overall survival
PFS: Progression-free survival
ORR: Objective response rate
TIME: Tumor immune microenvironment
YUHS: Yonsei University Health System
SPIRIT: Standard Protocol Items: Recommendations for Interventional Trials
RECIST: Response evaluation criteria for solid tumors
INR: International normalized ratio
ULN: Upper limit of normal
NYHA: New York Heart Association
HIV: Human immunodeficiency virus
AIDS: Acquired immunodeficiency syndrome
CTCAE: Common Terminology Criteria for Adverse Events
HRs: Hazard ratios
CI: Confidence intervals
IRB: Institutional Review Board
